#### Evaluation

Participants have to complete the following two questionnaires on the study website: 1) the baseline questionnaire (T0) and 2) the follow-up questionnaire 3 months after baseline (T1). The baseline questionnaire will assess the following demographics: gender, age, marital status, education, occupation, ethnicity, weight and height. Participants’ PA level will be assessed using a validated questionnaire [39]. The psychosocial determinants of the I-Change Model related to PA (intention, attitude, social influences, self-efficacy) will be assessed on a 7-point Likert scale [27]. The 3-month follow-up questionnaire consists of PA level reassessment as well as two I-Change Model variables, intention and self-efficacy. In addition, the follow-up questionnaire also consists of process evaluation questions in order to evaluate participants’ opinion of the intervention.

#### Sample size and data analysis

##### Sample size

The sample size was calculated using the G*Power software platform [40]. According to a mixed plan 2 (intervention group, control group) × 2 (baseline, 3-month follow-up), assuming a statistical power of 0.80, an alpha value of 0.05 and a moderate correlation (*r* = 0.5) between baseline and 3-month follow-up PA measures, a total sample size of 200 participants is required to detect a small effect size (*f* = .10). Statistical analysis using Statistical Package for the Social Sciences (SPSS) software (version 21) will be performed in line with the study’s objectives.

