Systematic reviews [14, 15] and meta-analyses [16, 17] have shown promising findings of web-based computer-tailored interventions in modifying PA behaviour. For instance, Krebs et al.’s meta-analysis of 25 studies showed a pooled mean effect size (Hedges’ *g*) of 0.16 (*p* < 0.001), and that 43 % of participants receiving a tailored intervention adhered to the PA recommendations at follow-up compared to 34 % in the control group [16]. Meta-analyses highlighted some characteristics that increase the likelihood of positive results [16, 18]. Using dynamically tailored interventions (i.e. updating feedback to reflect a person’s changes) [16], designing PA messages based on social-cognitive theories [18] and using more behaviour change techniques [18] should all be considered in developing such interventions. Moreover, recent studies have shown that a web-based computer-tailored intervention can be cost-effective in the PA domain [19] and in other health-related behaviours as well [20]. Therefore, a web-based computer-tailored intervention was developed to improve PA levels among Canadian adults particularly women and people with low-to moderate-education levels.

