### Baseline characteristics

Among the 2790 Quebec City PURE participants, 1269 were eligible to participate in the present study, of which 244 actually signed up. The socio-demographic and clinical characteristics of these 244 participants are described in Table 1. Participants had a mean age of 56 years, were mostly women (67.6 %) and have completed their college/university degree (83.6 %). Half of the population were overweight or obese, 12 % had hypertension and 2 % diabetes.

**Table 1 Tab1:** Characteristics of the randomized participants

Number of participants, *n*	244		
Mean age (*SD*), [range], years	56.3	(7.0)	[39–70]
Gender, *n* (%)			
female	165	(67.6)	-
male	79	(32.4)	-
Highest education level completed, *n* (%)			
high school	40	(16.4)	-
college/university	204	(83.6)	-
Smoking behaviour, *n* (%)			
current	14	(5.7)	-
never	127	(52.0)	-
former	103	(42.2)	-
Body mass index, *n* (%), kg/m^2^			
underweight (16.5-17.99)	2	(0.8)	-
normal (18–25)	112	(45.9)	-
overweight (25.01–29.99)	90	(36.9)	-
obese (30+)	40	(16.4)	-
Mean blood pressure (*SD*), [range], mm Hg			
systolic	127.0	(18.3)	[85–189]
diastolic	80.0	(11.0)	[55–117]
Mean low-density lipoprotein level (*SD*), [range], mmol/L	3.01	(0.8)	[1.21–5.57]
Mean high-density lipoprotein level (*SD*), [range], mmol/L	1.66	(0.44)	[.83–3.20]
Mean apolipoprotein B level (*SD*), [range], mmol/L	0.91	(0.24)	[.32–1.65]
Mean glycemia level (*SD*), [range], mmol/L	5.0	(0.7)	[3.7–10.2]
Participants reported risk factors, *n* (%)			
Hypertension	29	(11.9)	-
Diabetes	5	(2.0)	-
Medications, *n* (%)			
Anti-hypertensive medication	26	(10.7)	-
Hypoglycemic medication	2	(0.8)	-

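### The 80% power for a small effect (f = .10) is power for a 0.40 SD between-arm difference in change, not the 0.20 SD that a small f denotes for two groups

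*Protocol article*

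**What the plan says.** The Sample size section of the protocol article names the tool ("The sample size was calculated using the G*Power software platform") and the design ("According to a mixed plan 2 (intervention group, control group) × 2 (baseline, 3-month follow-up"). It lists the inputs as "assuming a statistical power of 0.80, an alpha value of 0.05 and a moderate correlation", r = 0.5, this being the correlation "between baseline and 3-month follow-up PA measures". It concludes that "a total sample size of 200 participants is required to detect a small effect size", given as f = .10. It does not translate f into SD units or minutes per week, and it gives no reason for choosing .10.

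The rationale section on web-based computer tailoring reports earlier evidence: a "meta-analysis of 25 studies showed a pooled mean effect size" (Hedges' g) of 0.16. The sample size section does not refer to this figure. The baseline table shows that 244 people were randomised.

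**The concern.** A reader who sees f = .10 called small will take it in the usual two-group sense, where f is half the standardised mean difference and .10 means 0.20 SD. A two-group comparison at that effect needs nearly 800 participants, so 200 looks too few. Either the number is wrong, or f is measured on another scale and the label does not carry over.

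The practical stake is how a non-significant efficacy result is read. Efficacy on physical activity is the first objective. If readers believe the trial had 80% power for a small effect, they may take a null result as evidence that no small effect exists, and carry that into the decision about the larger trial that this one is meant to inform.

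**Working it through.** **Inputs from the protocol article:** 2 × 2 mixed design, power 0.80, alpha 0.05, r = 0.5, f = .10, N = 200 (Sample size); 244 randomised (Baseline characteristics); g = 0.16 (rationale).

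**Assumptions:** 1:1 allocation (no ratio is stated), a two-sided test, equal variance at both time points, no loss to follow-up, and g read in units of this trial's physical activity SD.

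**Step 1. Reproduce the stated N.** For G*Power's within-between interaction, with m = 2 measurements, λ = f² × N × m/(1 − r), tested on 1 and N − 2 degrees of freedom.
- N = 198: λ = 0.01 × 198 × 2/0.5 = 7.92, power 0.7997
- N = 200: λ = 0.01 × 200 × 2/0.5 = 8.00, power 0.804

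The smallest even N reaching 0.80 is 200, so the stated figure is reproduced exactly. Other readings of f = .10 do not give it: the between-factor test needs 592, and a plain two-group comparison (0.20 SD) needs 788.

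**Step 2. What f = .10 means in that test.** In a 2 × 2 interaction, f is the common size of the four cell deviations, in SD units. With deviations of ±0.10, one arm changes by +0.20 SD relative to the main effects and the other by −0.20 SD. The difference in change is 4 × 0.10 = 0.40 SD.

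**Step 3. Cross-check.** The SD of change is √(2(1 − r)) = √(2 × 0.5) = 1 SD. A two-sample t-test on change with 100 per arm and a 0.40 SD difference has power 0.804, as in Step 1. A simulation of the same set-up gave 0.807.

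**Step 4. Power for smaller differences.** For a difference d, the interaction f is d/4. This gives λ = N × d²/4 for change scores. With baseline adjustment the residual variance is 1 − r² = 0.75, so λ = N × d²/(4 × 0.75).

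| Difference (SD) | Analysed | Power, change | Power, baseline-adjusted |
|---|---|---|---|
| 0.40 | 200 | 80.4% | 90.1% |
| 0.20 | 200 | 29.1% | 36.9% |
| 0.20 | 244 | 34.3% | 43.5% |
| 0.16 | 200 | 20.3% | 25.5% |
| 0.16 | 244 | 23.8% | 30.1% |

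As an example, 0.16 SD with 200 on change has λ = 200 × 0.0256/4 = 1.28.

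The ratio to the cited pooled effect is 0.40/0.16 = 2.5. For 80% power at 0.16 SD the total would be about 1,230 on change or about 920 with baseline adjustment.

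**Step 5. Difference detectable with 80% power.** On change: 0.40 SD with 200 analysed and 0.36 SD with 244. With baseline adjustment: about 0.35 SD and 0.32 SD. Values of 0.34 and 0.31 SD would fall just short, at 78.9% and 79.5%.

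**The case against.** Several points on the other side carry weight.

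- **The arithmetic is right.** Software, design, alpha, power, r and f are all given, and they return 200. A reader might infer that the sample size was miscalculated; it was not. The fault lies in the word small, which belongs to a different scale.
- **The protocol does not adopt g = 0.16 as its planning effect.** A reader might infer that the trial is powered at 20–30% for the effect it expects. The text does not support this. The rationale reports a pooled literature figure, then lists features that favour larger effects, and the Discussion mentions establishing larger effect sizes. What stands is narrower: this is the only standardised effect the article cites, and nothing in it gives a reason to expect 0.40 SD.
- **The scale of g is not known.** The article does not say how the meta-analysis standardised its outcomes or over which measures, so reading g as 0.16 SD of this trial's measure is an assumption. The cited adherence contrast (43% against 34%) concerns a different outcome from the one powered, and the point does not rest on it.
- **Baseline adjustment raises power.** It does, but only to 30% at 0.16 SD with all 244. It is also not the stated plan: the efficacy section adjusts for physical activity variables only where they differ significantly between arms.
- **The trial precedes a full-scale RCT.** The abstract and conclusion say so, and recruitment exceeded 200. This lowers the seriousness. It does not remove the point, because efficacy is the first objective and a formal power claim is made for it.

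A reader might also want the difference in minutes per week or the power after dropout. The article gives neither an SD of weekly activity nor an expected loss rate, so neither can be derived from it.

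**Conclusion.** The point holds as one of labelling and interpretation. The stated 80% power is for a between-arm difference in change of 0.40 SD. For the 0.20 SD usually meant by a small f = .10, power with 200 is about 29% on change and about 37% if baseline-adjusted. For the pooled effect cited in the rationale it is about 20% with 200 and 24% with 244 analysed, or 26% and 30% if baseline-adjusted.

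The equivalence of f = .10 and 0.40 SD follows from the interaction formula. The power figures also need 1:1 allocation, a two-sided test and no attrition, and those for 0.16 SD need g to be read in this trial's SD units. It should be fixed, but it does not invalidate the design.

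**What to change.** Reword the Sample size section along these lines:

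> *Two hundred participants with 3-month data give 80% power for a between-arm difference in change of 0.40 SD (0.36 SD if all 244 respond), assuming r = 0.5, a two-sided alpha of 0.05 and equal allocation. Power for a difference of 0.16 SD, the size of the pooled effect cited in the rationale if it applies on this scale, is about 20% with 200 and 24% with 244. A non-significant result does not exclude effects below about 0.4 SD.*

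Delete the word small, or qualify it by saying that f is on the interaction scale. If baseline-adjusted detectable differences are added, give about 0.35 SD for 200 and 0.32 SD for 244, and say that they assume an adjustment not currently in the plan.

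The cost is a less favourable stated sensitivity. No participants are added, and neither the outcome nor the analysis changes.

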##### Efficacy of the intervention

The efficacy of the PA intervention, 3 months after baseline, will be assessed with linear mixed models. This statistical analysis is very well suited for modelling data containing repeated measures from several participants [41] and has the advantage of providing better capabilities to handle missing observations compared to more traditional approaches, such as repeated measures ANOVA [42, 43]. It is essentially a general linear model, with the addition of random effects to account for the two sources of variability, within (e.g. time 0, time 1)- and between (e.g. intervention, waiting list control group)-subject variance [41]. Analysis will be adjusted for socio-demographic characteristics and PA variables that significantly differ between study arms at baseline.

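### As most naturally read, the 2 × 2 mixed model compares mean change and adjusts for baseline PA only after a significant imbalance; this is valid but less efficient than always adjusting for it.

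*Protocol article*

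**What the plan says.** Protocol article, Sample size. The design behind the calculation is introduced by "According to a mixed plan 2 (intervention group, control group) × 2 (baseline, 3-month follow-up". Power is set at 0.80 and alpha at 0.05. The calculation further takes "a moderate correlation (*r* = 0.5) between baseline and 3-month follow-up PA measures". For f = 0.10, described as small, the stated total is 200.

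Protocol article, Efficacy of the intervention: "The efficacy of the PA intervention, 3 months after baseline, will be assessed with linear mixed models". This section gives time 0 and time 1 as the example of within-subject variability, so T0 PA enters as a response. It then limits adjustment to socio-demographic and PA variables that differ significantly between the arms at baseline.

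The section does not list the fixed effects, name an arm × time term, or say whether the T0 means are free or constrained to be equal. Under Session one, the baseline measurement is placed inside the first intervention session. Objectives and design describes how participants were randomized but not when they learned their allocation.

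**The concern.** If both time points are responses and the T0 means are free in each arm, the arm × time estimate with complete data is the difference between arms in mean change. Subtracting T0 gives it a weight of 1. When the SDs are equal, the weight that minimises the variance is the correlation, here 0.5, so the change score over-corrects and adds noise.

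The adjustment rule does not repair this. It brings T0 PA in only after a significant chance imbalance, although T0 PA is collected on everyone and is prognostic by the plan's own assumption. At stake is power that could be had from data already collected.

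**Working it through.** **Inputs.** From Sample size: 2 arms × 2 times, f = 0.10, r = 0.5, alpha 0.05, power 0.80, total 200. From Baseline characteristics: 244 participants. Assumed, because the article does not state them: 1:1 allocation, a two-sided test, complete T1 data and, except in step 5, equal SDs (σ) at T0 and T1.

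**1. Reproduce the plan's figure.** For the arm × time test, λ = f²·N·m/(1 − r) with m = 2 and 1 and N − 2 degrees of freedom.
- At N = 200, λ = 0.01 × 200 × 2 / 0.5 = 8, and power is 0.8036. At N = 198 it is 0.7997.
- The smallest even total is therefore 200, as stated. The between-arm version of the calculation needs 592, so the plan was sized on the arm × time test.

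**2. Translate f.** The variance of change is 2(1 − r)σ² = 1.00σ². A difference in mean change of d SDs gives λ = d²·N/4 = 50d² at N = 200. Setting 50d² = 8 gives d = 0.40 SD.

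**3. Compare variances (per participant, equal SDs).**
- Change: 2(1 − r)σ² = 1.00σ²
- T0-adjusted: (1 − r²)σ² = 0.75σ²
- Ratio: (1 + r)/2 = 0.75, a 25% loss of precision (inverse variance)

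With other correlations the loss is 35% at r = 0.3, 30% at 0.4, 20% at 0.6, 15% at 0.7 and 10% at 0.8.

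**4. Power for 0.40 SD.**

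| Total analysed | Change | T0-adjusted |
|---|---|---|
| 150 | 0.682 | 0.802 |
| 200 | 0.804 | 0.901 |
| 244 | 0.875 | 0.949 |

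The adjusted analysis reaches 80% power with 150 in total, against 200.

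**5. Relax equal SDs.** With T0 SD s₀ and T1 SD s₁, the variance of change is s₀² + s₁² − 2r·s₀·s₁ and the adjusted variance is s₁²(1 − r²). At r = 0.5 and s₁ = 1, the adjusted variance is 0.75 throughout:

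| s₀/s₁ | Variance of change | Loss |
|---|---|---|
| 1.0 | 1.00 | 25% |
| 0.8 | 0.64 + 1 − 0.80 = 0.84 | 1 − 0.75/0.84 = 11% |
| 0.7 | 0.49 + 1 − 0.70 = 0.79 | 1 − 0.75/0.79 = 5% |
| 0.5 | 0.25 + 1 − 0.50 = 0.75 | 0% |

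The article gives no PA SDs, so these ratios are illustrative.

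**6. Simulation (N = 200, r = 0.5, equal SDs, complete data).**
- The mixed model with free T0 means gave an arm × time estimate equal to the difference in mean change to rounding error (mean SE 0.141).
- With T0 means constrained equal, the mean SE was 0.122, a variance ratio of 0.749.
- Regressing T1 on arm and T0 gave an empirical variance ratio of 0.758 against change.
- Adding T0 PA as a main-effect covariate to the free-means model left the arm × time estimate identical to the change comparison. Read that way, the conditional rule does not recover the precision even when it is triggered.

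**The case against.** The strongest objection is that the article never writes out the fixed effects. A constrained-baseline model is also a linear mixed model with T0 and T1 as responses, so the wording permits it, and a full specification may be in a document not shown. A sample-size calculation does not by itself fix the later model. This stands as a limit on certainty: free T0 means are the natural reading, not a stated fact. It does not answer the adjustment rule, which is stated and makes use of T0 PA depend on a significant imbalance.

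Second, nothing here is invalid, since the sample size and the test match. This also stands, and the point is one of efficiency only.

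Third, 25% is not a fixed figure. Participant eligibility and recruitment admits only people not in regular moderate- to vigorous-intensity PA, which may compress the T0 spread. Step 5 shows how quickly the loss then shrinks.

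Three stronger readings are tempting and are not supported:
- **The change comparison is biased, by imbalance or regression to the mean.** Under randomization both estimators are unbiased, and regression to the mean affects the arms equally in expectation. What adjustment adds is protection against the imbalance that happens to occur.
- **The trial is underpowered because of this model.** The 200 already pays for the change-score variance, and 244 were randomized. The pooled effect of 0.16 cited in the background is not the planning effect. Adjustment would raise power for 0.16 SD at 244 only from 24% to 30%, so it would not settle that separate question.
- **Arm is treated as a random effect.** The wording "with the addition of random effects to account for the two sources of variability" is followed by loose examples of within- and between-subject variance. It does not say that arm is random.

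**Conclusion.** The point holds as a loss of efficiency on the natural reading of the plan. At r = 0.5 with equal SDs, the planned test has variance 1.00 against 0.75, and power for 0.40 SD with 200 analysed is 80% where 90% is available. The loss is larger if r is below 0.5 and smaller if r is higher or if the T0 SD is below the T1 SD (about 11% at a ratio of 0.8, 5% at 0.7).

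The size rests on 1:1 allocation, a two-sided test and complete data; with missing T1 values, equality with the change comparison is only approximate. The planned analysis is valid and its sample size is correctly derived. The change is worth making because it replaces a data-dependent rule with a fixed one and uses data already collected.

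**What to change.** Drop the significance trigger for PA variables and state that T0 PA is adjusted for whatever the baseline comparison shows. Specify one of:

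1. T1 PA regressed on arm and T0 PA; or
2. a mixed model with T0 and T1 PA as responses, fixed effects for time and arm × time, no arm main effect (so the T0 mean is common to both arms), and an unstructured residual covariance. Add no participant random effect: with two time points the unstructured matrix already uses all three covariance parameters, and a further random effect is not identifiable.

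The second option keeps the plan's stated reason for choosing mixed models, the handling of missing observations. In either case, report the adjusted T1 difference with its 95% CI.

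Before adopting the second option, confirm that T0 was completed before participants knew their allocation. The article leaves this open, and if it was not so, the equal-means constraint could itself introduce bias.

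The cost is a change of analysis wording and that one check of trial conduct. No new data are needed, and both models can be fitted in the named software.

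### Covariates are selected by a baseline significance test; the plan should instead name them in advance and always adjust 3-month PA for baseline PA

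*Protocol article*

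**What the plan says.** Under Efficacy of the intervention, the protocol article plans that "The efficacy of the PA intervention, 3 months after baseline, will be assessed with linear mixed models". The repeated measures are baseline (T0) and 3-month (T1) PA, "with the addition of random effects to account for the two sources of variability, within (e.g. time 0, time 1") and between participants. T0 PA is therefore part of the response. The covariate rule closes that section: "Analysis will be adjusted for socio-demographic characteristics and PA variables that significantly differ between study arms at baseline". No covariate is named in advance, and the article does not say whether covariates enter as main effects or with a time interaction.

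The Sample size section is built on an arm-by-time layout: "According to a mixed plan 2 (intervention group, control group") by two occasions, "assuming a statistical power of 0.80, an alpha value of 0.05" and "a moderate correlation (*r* = 0.5) between baseline and 3-month follow-up PA measures". It concludes that "a total sample size of 200 participants is required to detect a small effect size" of f = 0.10. Under Baseline characteristics, 1269 people were eligible, "of which 244 actually signed up". The Evaluation section lists eight demographic variables collected at T0, plus PA level.

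**The concern.** The rule has one defect that is plain from the text and one that depends on how the model is written.

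First, a significant baseline difference between randomised arms says nothing about prognostic value. A strong predictor of PA that happens to be balanced is left out, and a weak one that happens to be imbalanced is put in. The efficacy model also stays open until the arms have been compared.

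Second, in an arm-by-time model a covariate that is constant over time, entered as a main effect, explains differences between people but not change within people. The effect could then be reported as adjusted for baseline differences although the adjustment did almost nothing to it. The variable that matters most is T0 PA: the rule expressly covers PA variables, yet T0 PA is already a response.

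**Working it through.** **Inputs.** r = 0.5, f = 0.10, alpha 0.05, power 0.80 and N = 200 (Sample size); 244 randomised (Baseline characteristics); eight demographics plus PA (Evaluation). Assumed: 122 per arm, equal variance at T0 and T1, normal outcomes.

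**1. The plan's own figure.** For the within-between interaction, lambda = N × m × f² / (1 − r) = 200 × 2 × 0.01 / 0.5 = 8. With 1 and 198 degrees of freedom the power is 0.804, so 200 is reproduced. The between-factor version needs 592. The sizing therefore corresponds to the arm-by-time interaction. The SD of change is sqrt(2(1 − 0.5)) = 1 SD, and with 100 per arm lambda = d² × 50 = 8 gives d = 0.40 SD, the design effect.

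**2. How often the rule selects something.** 1 − 0.95⁹ = 0.37 for nine variables, if independent.

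**3. What main-effect adjustment does.** Mixed models were fitted to one simulated data set of 244 with both measurements present for everyone.

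| Covariate terms | Arm-by-time estimate |
|---|---|
| none | 0.7070 |
| demographic-type covariate, main effect | 0.7070 |
| T0 PA, main effect | 0.7070 |
| demographic-type covariate × time | 0.634 |

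The first three equal the raw difference in mean change. With 10% to 30% of T1 missing, main-effect covariates moved the estimate by a mean of only 0.01 to 0.03 outcome units (12 simulated trials per rate).

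**4. Size of the uncorrected imbalance in T0 PA.** The smallest significant difference at N = 244 is 1.96 × sqrt(4/244) = 0.251 SD. The change-based estimate is then off by −(1 − r) × 0.251 = −0.125 SD, which is 0.125/0.40 = 31% of the design effect. In 8000 simulated trials with a true effect of 0.40 SD, those with a significant T0 imbalance gave a mean arm-by-time estimate of 0.24 when the intervention arm started higher and 0.55 when it started lower. Regressing T1 on arm and T0 gave 0.39 and 0.40.

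**5. False positives.** Rates in simulated null trials, restricted to those where T0 PA differs at p < 0.05:

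| r | Change, unadjusted | T0 PA also a main effect | T1 on arm and T0 PA |
|---|---|---|---|
| 0.3 | 24% | 31% | 5% |
| 0.5 | 19% | 23% | 5% |
| 0.7 | 13% | 14% | 5% |

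These average over significant imbalances of every size. Exactly at the threshold with r = 0.5 the rate is lower. Given z = 1.96 for T0, the change statistic has mean −sqrt((1 − r)/2) × 1.96 = −0.98 and SD sqrt(1 − 0.25) = 0.866, so the near-tail probability is Φ((−1.96 + 0.98)/0.866) = Φ(−1.13), about 13%.

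The second column exceeds the first because entering T0 PA as a covariate drives the random-intercept variance to zero. The standard error shrinks by sqrt((3 + r)/4) = 0.935 at r = 0.5, while the estimate does not move.

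Over all null trials, 20,000 at each r, the rate was 4.8% unadjusted and 5.0% under the rule at r = 0.5 (5.1% and 5.5% at r = 0.3).

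**6. Gain from always adjusting for T0 PA.** The residual SD is sqrt(1 − 0.5²) = 0.866 against 1.0 for change. With 100 per arm and a 0.40 SD effect, power is Φ(0.40/(1.0 × sqrt(2/100)) − 1.96) = 0.81 for change and Φ(0.40/(0.866 × sqrt(2/100)) − 1.96) = 0.90 with adjustment.

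**The case against.** A reader might infer that the planned adjustment cannot move the treatment estimate, so that any imbalance the rule detects stays in the result. The article does not support that.

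- Neither main-effect entry nor the arm-by-time contrast is written down, and an article may leave the specification of terms to a fuller document. The hypothesis in the Discussion compares PA levels at 3 months. For a T1 contrast from the same model, a main-effect covariate does move the estimate (from 0.152 to 0.048 in one simulated data set with age 0.4 SD apart). Against this, only the interaction reproduces the sample size of 200.
- Exact invariance needs complete pairs, and the article anticipates missing observations. The resulting shift is small.
- A demographic that affects PA equally at T0 and T1 already cancels in the change (simulated mean bias 0.0005). What remains concerns T0 PA and predictors of change.

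Nor should the 19% be charged to the rule. It comes from analysing change when T0 PA is imbalanced, which happens in about 5% of trials. The rule adds the step from 19% to 23%, and only if the PA variables include T0 PA itself and it enters as a main effect. The overall error rate hardly moves.

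These objections limit the second defect. They do not touch the first, which is a stated rule and not an omission.

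**Conclusion.** The point holds in two parts of different strength. Selecting covariates by a baseline significance test is a fault in the text as it stands, whatever the model. The claim that the adjustment would have little or no effect is conditional on an arm-by-time test with main-effect covariates. On that reading, an imbalance in T0 PA, or in a covariate that predicts change, goes uncorrected. The consequence is a distorted estimate in the minority of trials where T0 PA is imbalanced, about 31% of the design effect at the threshold, rather than an inflated error rate overall. The sizes rest on r = 0.5, equal arms and equal variances. The sample size of 200 is not in question. The change should be made; the design does not depend on it.

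**What to change.** Replace the covariate sentence so that it does four things:

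1. Deletes selection by baseline significance.
2. Always adjusts T1 PA for T0 PA, whatever the observed balance, by ANCOVA on T1 or by a mixed model with T0 and T1 as responses and a common baseline mean across arms. The mixed model also keeps participants without T1.
3. Names age, sex and education as covariates before arm-level data are seen, entered so that they act on T1 PA or on change (in the T1 model, or as covariate-by-time terms).
4. Rules out entering T0 PA as a covariate in any model where it is also a response.

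Item 2 is essential: covariate-by-time terms for demographics alone leave an imbalance in T0 PA uncorrected. The cost is a short edit and a few degrees of freedom, and every variable is already collected. The one downside is that an imbalanced covariate outside the list is examined only in a sensitivity analysis.
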